## Discussion

This study will test Behavioral Activation (BA) as a nursing intervention in an inpatient elderly population. The study is innovative in two aspects. First, in previous studies psychologists with Master’s degrees carried out this intervention [10,11,18]. In our study, BA has been adapted to make it a nursing intervention – the SAM – to be carried out by registered nurses [28]. This makes BA more accessible for a larger group of patients.

Second, to our knowledge, most of the research on BA has mainly been conducted in outpatient adult populations. Only one other study [18] was executed in an inpatient adult population (N = 25) and, as far as we are aware, there are no studies in elderly inpatient populations. Studies in the elderly population are relatively scarce and have focused on outpatients [42,43] or depression in combination with dementia [44,45]. To our knowledge, this is the first BA effect study in an elderly inpatient population worldwide.

In addition to the innovative nature of this study, there are some difficulties concerning the study design. First, the study is vulnerable to selection bias. The SAM will be implemented in five mental health care units, and decisions regarding patient inclusion will depend partially on the anticipated efforts of the staff nurses. In order to minimize selection bias, the researcher will make an initial selection of eligible patients. Despite this, however, selection bias cannot be ruled out entirely, because it is ultimately the nurse who must motivate the patient to participate in the study, and this is expected to depend on the nurses’ belief that the SAM will be helpful for the patient. This may lead to selection bias in the experimental group, while the selection of patients in the control group will probably be free of bias. We will correct for any differences between the two groups in our statistical procedures.

This study will furthermore be vulnerable to information bias because a blind trial at intervention level is not possible. In order to avoid information bias, only self-report scales will be used in this study.

Finally, the standardized execution of the intervention is a point of concern. The SAM will be implemented at five units for elderly persons with psychiatric disorders. Although the SAM is presented as a highly prescriptive intervention, we expect that – due to differences in patient characteristics – individual variations in the execution of the SAM may occur that will be difficult for the researchers to control. Coaching meetings will be organized to promote treatment integrity.

### Ethical considerations

In the experimental condition, the SAM will be implemented as an adjunctive treatment modality. This means that patients with MDD will have an opportunity to benefit from the SAM while receiving treatment as usual. Although the study is intended for a broad category of patients, some patients will be excluded from the study, even though the nurses believe they could benefit from the SAM or parts thereof. These patients will also have an opportunity to engage in the SAM, but they will not be included in the study.

The SAM will be implemented in the control group units after all the patients have been included.

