### The units and randomization

The study will include ten mental health care units, which will be randomized to the experimental (SAM) or control (TAU) conditions. The following inclusion criteria will be used to select the units: (1) the units must specialize in the treatment of elderly patients with psychiatric disorders; (2) there must be at least three registered nurses (RNs) available who are able and willing to execute the intervention. Units that specialize in a specific disorder or treatment method (e.g. Electro Convulsion Therapy) will be excluded from the study.

Within each mental health institute, the aim is to find two units which are comparable. Matching of units is based on two criteria which will be applied in the following order: (1) level of restraint – both units should either be open or closed; (2) the presence of other treatments containing elements of the SAM, i.e. occupational therapy (because it focuses on activation), psychological treatment (because it focuses on influencing cognition).

For matching purposes, staff members at the participating units will be asked to fill in a self-developed evaluation form providing information on the specific features of the unit. This form includes a number of general questions concerning characteristics of the patient group, followed by more specific questions about the treatment program and level of restraint.

After matching the units into pairs, one unit will be allocated to the experimental condition and the other to the control condition. Allocation will be performed by an independent researcher ([name]) who will not maintain contact with the participating units. A random allocation generator will be used.

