### Recruitment of the study sample

The participating units will keep a list of all newly admitted patients and their primary diagnosis. All patients older than 60 with a primary diagnosis of MDD will be approached by a staff member and informed about the study. Once verbal consent is obtained and there are no cognitive problems according to the Minimal Mental State Examination (MMSE score ≥ 23) [20], the patients will be approached by one of the researchers. Confirmation of the psychiatric diagnosis will be executed by means of a diagnostic interview using the MINI Plus, a standardized instrument to assess psychiatric disorders according to the DSM-IV criteria [21]. Patients who satisfy the inclusion criteria will then be included in the study. Due to the nature of the intervention, it will not be possible to perform the study as either a single-blind or double-blind trial.

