### Intervention

We developed the Systematic Activation Method (SAM) as a brief behavioral nursing intervention which focuses on increasing a positive mood change by increasing the number of positive activities. The SAM is based on Behavioral Activation (BA), developed by Lewinsohn and colleagues [22-27] and Hopko et al. [18]. The underlying assumption is that positive reinforcement of a low response rate acts as an eliciting stimulus for depressive behaviors and serves as a sufficient explanation for inactivity in a depressed individual [27]. The SAM is presented as a brief seven-week course. In order to make the SAM accessible for the elderly inpatient population, we have made some adjustments to the existing BA protocols. First, the goals of each session are described in the course book. This differs from the existing protocols, in which the first session is used for mutual goal setting. It is difficult to describe the overall goals of treatment for inpatient elderly with MDD; that is why the goals have been described at the beginning of each session. Second, the course is presented as a nursing intervention instead of a psychological intervention in order to increase its accessibility. Third, we simplified the activity logs to avoid overloading the patients. Fourth, the duration of the intervention has been shortened to seven weeks, in contrast to the existing treatment protocols, which last between eight and 15 weeks.

The SAM consists of six sequential steps: 1) monitoring the patient’s mood; 2) having the patient execute pleasant activities, randomly selected from an existing list of 49 activities [25]; 3) having the patient develop a positive activity plan; 4) having the patient explore how to use external resources; 5) setting up an activity experiment; 6) evaluation and consolidation. There is a one-week time interval for each step except the third step (developing a positive activity plan), for which two one-week intervals are required. If necessary, the time interval between the sessions can be reduced or extend. Each session is highly structured and starts with a review of the patient’s homework. After that, the nurse and patient discuss the central theme of the session and the patient is given his or her homework assignments for the coming week. The SAM is described in more detail by Clignet, Van Meijel, Van Straten, Lampe and Cuijpers [28].

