### Control group

The control group will receive Treatment As Usual (TAU). The most common treatment for patients with MDD is a combination of medication, occupational therapy and a form of psychological treatment such as Cognitive Behavioral Therapy (CBT) or Problem Solving Treatment (PST). Nursing care focuses on assisting patients in their self-care activities, and encouraging them to participate in the unit’s daily activity program. Nurses also discuss the patient’s overall progress on a regular basis (weekly or biweekly). TAU is recorded at unit level. Before participating in the study, the units describe their treatment program for MDD using a structured form developed by the authors. This form is based on the NICE standard for MDD [7] and the Dutch guideline for MDD [29].

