### Assessment

All patients will be assessed at baseline, after eight weeks, and after six months. Each assessment will involve patients filling in a questionnaire. At baseline, we will collect demographic data (gender, social status, education, and ethnicity) and some information about the disease history (former episodes of MDD, frequency and nature of former treatments [outpatient treatments and/or clinical admittance], and psychiatric co-morbidity).

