### Primary outcome

Our primary outcome is the level of depression. This is measured by means of the Beck Depression Inventory, second edition (BDI-II-NL) [30,31]. The BDI-II is a self-report scale which contains 21 items clustered in four response categories. The BDI-II is divided into two components, an affective component (e.g. mood) and a physical component (e.g. loss of appetite). The cut off scores are: 0 – 13 for minimal depression, 14 – 19 for mild depression, 20 – 28 for moderate depression, and 29 – 63 for severe depression. The Dutch version of the BDI-II has a high internal consistency (Chronbach’s α ≥ 0.90) and a strong correlation with other depression instruments [32].

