### Sample size

Effect sizes (d) will be used to calculate the sample size. A meta-analysis by Cuijpers et al. [10] found an overall effect size of d = 0.87 in favor of Behavioral Activation (BA) compared to a waiting list condition. A study in an inpatient population found an effect size of d = 0.73 in favor of BA compared to supportive therapy [18].

Our study will be performed in an inpatient elderly population with severe MDD. Because of the large effect sizes in previous studies, an effect size of d = 0.7 is expected. With α = 0.05 and a power (1-β) of 0.8, 34 patients are needed per condition. In other studies [10,40], the dropout rate shows a large variability (2% – 50%). For this study, we assume an average drop-out rate of 25%. Another rule of the thumb is to increase the study population by 25% when patients are randomized at unit level. That means that 51 patients are required for each condition. In total, 102 patients will be included in this study. The sample size was calculated using the G*power 3.0 software program [41].

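### Control units may start SAM once enrolment closes, with no wait for the 8-week and 6-month assessments, so late-enrolled control patients could receive it before their outcome is measured

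*Protocol article*

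**What the plan says.** The condition for giving SAM to the control units is in the Ethical considerations section of the protocol article: "The SAM will be implemented in the control group units after all the patients have been included". No other section adds a condition.

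Recruitment of the study sample shows what inclusion means. After consent, cognitive screening and the diagnostic interview, "Patients who satisfy the inclusion criteria will then be included in the study". This is entry to the trial, before any follow-up.

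On follow-up, the Assessment section says: "All patients will be assessed at baseline, after eight weeks, and after six months". Table 1 counts both later time points from T0. The primary outcome, the BDI-II-NL, is collected at T0, T1 and T2. The Activity Log and the TiC-P cost questionnaire are collected only at T0 and T2.

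On the comparator, the Control group section says: "The control group will receive Treatment As Usual (TAU"). TAU is recorded at unit level, from a description that each unit gives before it takes part. On the length of the course, the Intervention section says: "The SAM is presented as a brief seven-week course".

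**The concern.** Read together, these sections leave a gap. When the last patient is enrolled, that patient still owes T1 and T2, and every control patient enrolled in the preceding six months still owes T2. Nothing in the article makes the control units wait for those assessments.

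Allocation is by unit, so roll-out would bring SAM to the very wards where the remaining control patients are treated. A control patient who receives SAM before T2 is still analysed as TAU. If SAM is effective, the difference between arms shrinks.

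T2 is the more exposed time point. It is also the only post-baseline measurement of costs and of activity level, and activity is what SAM sets out to raise.

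The article describes no record of SAM received by individual control patients. The intention-to-treat and completers-only analyses, and the methods for missing values, do not address exposure that was never recorded. The Discussion covers selection bias, information bias and treatment integrity, but not this.

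**Working it through.** **Inputs from the protocol article.** Effect size: "an effect size of d = 0.7 is expected" (Sample size). Alpha 0.05, power 0.80, 34 per condition before inflation and 51 after (Sample size). T1 at 8 weeks and T2 at 6 months after T0 (Table 1). Course length seven weeks (Intervention).

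**Inputs not given, so assumed.** Recruitment length R: even accrual over 18, 24 or 36 months. Roll-out on the day of last inclusion. No control patient discharged before receiving SAM. The last two are worst cases. Trial status gives an expected end of data collection but no start of recruitment, so R cannot be derived.

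**Step 1: the plan's own figure.** A two-sided two-sample t-test with d = 0.7, alpha 0.05 and power 0.80 needs 33.02 per arm, rounded up to 34. With 34 evaluable per arm the power is 0.81. Adding 25% for dropout and 25% for clustering gives 34 × 1.5 = 51. Both stated figures reproduce.

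**Step 2: control patients with an assessment pending at last inclusion.** Under even accrual the share is (time from T0 to assessment) / R. Eight weeks is 8 × 7 / 30.44 = 1.84 months.

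**Step 3: control patients who could complete the course before the assessment.** The course must fit between roll-out and assessment.
- Before T2: 6 months less seven weeks (7 × 7 / 30.44 = 1.61 months) leaves 4.39 months. The share is 4.39 / R.
- Before T1: eight weeks less seven leaves one week (0.23 months). The share is 0.23 / R.

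**Step 4: dilution.** If each patient in Step 3 gets the full SAM effect, d′ = 0.7 × (1 − share). Power is for 34 evaluable per arm and ignores clustering, as in Step 1.

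| R (months) | T2 pending | Could complete before T2 | d′ at T2 | Power at T2 | T1 pending | Could complete before T1 |
|---|---|---|---|---|---|---|
| 18 | 6/18 = 33% (17 of 51) | 4.39/18 = 24% (12) | 0.7 × 0.756 = 0.53 | 0.58 | 1.84/18 = 10% (5) | 0.23/18 = 1.3% (0.7) |
| 24 | 6/24 = 25% (13) | 4.39/24 = 18% (9) | 0.7 × 0.817 = 0.57 | 0.64 | 1.84/24 = 8% (4) | 0.23/24 = 1.0% (0.5) |
| 36 | 6/36 = 17% (9) | 4.39/36 = 12% (6) | 0.7 × 0.878 = 0.61 | 0.70 | 1.84/36 = 5% (3) | 0.23/36 = 0.6% (0.3) |

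Fewer than one control patient in 51 could complete a standard course before T1. Any effect there would come mainly from partial courses.

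**Step 5: with the rule changed.** If roll-out waits for the last control T2, the share is 0, d stays at 0.7 and the stated sample size is unaffected.

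**The case against.** The strongest reply is that the roll-out sentence sets an earliest time, not a date. Starting SAM in the control units after the last T2 would also satisfy it. A reader might infer that roll-out is scheduled before the last assessments, or that the roll-out rule and the follow-up schedule are incompatible. The article supports neither: one roll-out date can satisfy both. The sentence also concerns units and does not say that enrolled control patients will be offered SAM, while the Control group section assigns them TAU without a time limit. This part of the objection stands. What remains is that the only stated condition is the end of enrolment, so the rule allows the exposure.

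Second, a reader might apply the full SAM effect to everyone with T2 pending. That would give d = 0.7 × (1 − 6/R), or 0.47 to 0.58 for 18 to 36 months. This overstates the dilution. SAM is delivered on the ward by nurses who must first be trained, and a standard course takes seven weeks. Patients discharged before roll-out and not readmitted could not receive it there. This stands too, and the narrower shares in Step 3 are the better guide. They are indicative only: the article lets session intervals be shortened, and a partial course may have some effect.

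Third, the bias runs toward no difference, so it would not create a false-positive result. That is correct and lowers the gravity of the point. It does not remove it, because the trial is planned at 80% power and has little room for a diluted contrast.

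**Conclusion.** The concern holds as a gap in the roll-out rule. As written, the rule allows SAM into control units before follow-up there is complete, and the article describes neither a safeguard for enrolled control patients nor a record of their exposure. It does not show that contamination is planned or will occur.

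The consequence would be bias toward zero, mainly at T2. Its size cannot be fixed from the article. The limit of d at about 0.53 to 0.61 rests on even accrual over 18 to 36 months, roll-out on the day of last inclusion, no discharge, and the full SAM effect in everyone able to complete the course. Discharge and training time would make the loss smaller; shortened or partial courses would add to it.

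**What to change.** Reword the sentence in Ethical considerations so that SAM training and roll-out in the control units begin only after the last control patient's T2 assessment. This removes the exposure and leaves the sample size and analysis unchanged. The cost is one sentence, and control units wait up to about six months longer for SAM.

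If earlier roll-out is kept, record the roll-out date in each control unit and each control patient's SAM exposure, and prespecify a sensitivity analysis. That analysis should apply the same calendar cut-off to both arms. Dropping post-roll-out assessments from the control arm alone would make the arms differ in calendar period. The cost is an added exposure record and one further analysis, with fewer assessments in it. There is no need to change the primary time point on this account.

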#### Trial status

The research is ongoing at the moment. We estimate that data-gathering will be completed in October 2012.
